# 20. STATISTICAL ANALYSIS PLAN

## Analysis Sets

For this study, SIRO will consider the following analysis sets:

- **Intent‑to‑treat (ITT) Population:** All patients who received at least one dose of study drug.
- **Modified‑intent‑to‑treat (MITT) Population:** All patients who received study drug as per the protocol‑specified duration and had at least one efficacy assessment throughout the study.
- **Per Protocol (PP) Population:** All patients who complete the study visits per protocol without major protocol deviations.

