**Rescue medication:**

If the subject develops worsening of symptoms of Kala-azar, investigator may decide to use an alternative antileishmanial drug in appropriate doses or AmBisome 5 mg/kg IV on Days 1, 3, 5 and 7 as a rescue medication. In such situation, the subject will be discontinued from study.

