## Efficacy evaluation

- Patient will be considered eligible for efficacy evaluation if study drug has been administered and at least one efficacy assessment has been done.
- Failure of treatment is defined as the presence of any of the following conditions:

Presence of amastigotes on splenic smear examination

Treatment discontinuation due to intolerance

- Patients who discontinued the study drug before completing the total dosage due to a DLT will be considered non-evaluable.
- Non-evaluable patients who receive any dose of study drug will be included in the safety analysis.

Clinical status will be graded on a daily basis until the patient is hospitalized and at each visit thereafter.

- - - Timing of assessments: (applying the criteria for efficacy endpoint)

First assessment will be done at Day 30 after study drug administration

Second assessment on Day 45 ‑(only for patients who have a splenic aspirate score of +1 on Day 30) if the splenic score is 0, follow-up will be performed at 6 months after study drug administration and if the splenic score is +1 and above, no further follow-up will be performed.

If the splenic score is above +1 on Day 30 or Day 45 patient will be a treatment failure and no further follow-up will be performed.

At the end of 6 months after study drug administration, only if relapse is suspected – EOS visit.

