**Events NOT to be reported as AEs**

- Progression of underlying disease/study indication/lack of efficacy of the IP should NOT be reported as an AE/SAE.

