**Primary Efficacy Analysis:**

Non-inferiority will be assessed by looking at the lower end of a two sided 95% confidence interval (CI) of the difference Ptest - Pref (the difference in the proportions of patients achieving definitive cure in Amphomul^®^ (Ptest) and AmBisome (Pref). Non-inferiority will be only accepted if the lower limit of the two-sided 95% CI is greater than the non-inferiority margin of -0.10.

Non-inferiority will be tested for both MITT and PP population.

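### The non-inferiority test is run only in MITT and PP, which leave out patients whose infusion was stopped for toxicity and patients who died, were rescued or left before Day 30

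*Protocol*

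**What the plan says.** Section 20.1 defines MITT as "All patients who received study drug as per the" protocol-"specified duration and had at least one efficacy assessment throughout the study". PP is narrower: patients who complete the study visits without major deviations. ITT is everyone who received at least one dose.

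Section 20.2.2 sets the primary comparison, the difference in definitive cure against a margin of -0.10, and states: "Non-inferiority will be tested for both MITT and PP population". Section 20.2.3 assigns ITT to the safety analysis. No efficacy analysis in ITT is stated.

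Section 17.2 fixes the timing: "First assessment will be done at Day 30 after study drug administration". The same section lists "Treatment discontinuation due to intolerance" as a form of treatment failure, then says: "Patients who discontinued the study drug before completing the total dosage due to a DLT will be considered non-evaluable".

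For patients rescued because kala-azar worsens, the Study Summary says: "In such situation, the subject will be discontinued from study". Section 12.6.1 lists the withdrawal reasons: death, adverse event, lack of efficacy, consent withdrawal, investigator or sponsor decision, pregnancy and loss to follow-up.

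**The concern.** Both MITT conditions are met or missed after randomisation, and both can depend on the drug. Treatment is one infusion over 4 to 6 hours. If it is stopped for toxicity and not completed, the duration condition fails. If the patient dies, is rescued and discontinued, or leaves before the Day 30 visit, there is no efficacy assessment. PP drops the same patients, so agreement between MITT and PP gives no reassurance.

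The trial is open-label, and the investigator decides on stopping, rescue and withdrawal. If these early exits are more frequent on Amphomul, removing them narrows or hides a real deficit and makes non-inferiority easier to declare. If they are more frequent on AmBisome, the bias runs against Amphomul. Either way, the comparison is no longer between the randomised groups.

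**Working it through.** **The plan's own figures.** 400/0.80 = 500, 300/0.80 = 375 and 100/0.80 = 125, so the enrolment numbers reproduce. The 400 itself cannot be confirmed, because no common cure rate is given. At one-sided 0.025, power with 300:100 is 0.79 at a cure rate of 0.89 and 0.82 at 0.90, so the size fits a rate near 0.89 to 0.90. The point here does not depend on it.

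**Who is in the primary test, reading Sections 17.2, 20.1 and 20.2.2 together**

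| Patient | MITT | PP |
|---|---|---|
| Infusion stopped for toxicity, not completed | out (duration) | not a protocol completer |
| Rescued and discontinued before Day 30 | out (no assessment) | out |
| Died before Day 30 | out (no assessment) | out |
| Lost or withdrawn before Day 30 | out (no assessment) | out |
| Score above +1 at Day 30, or +1 and above at Day 45 | in, as failure | depends on how completion is read |
| Relapse before 6 months | in, as failure | depends on how completion is read |

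**Illustration.** The protocol gives no rates for early exits, so these are assumptions: 375 and 125 patients treated, 95% definitive cure in both arms among those retained, and excluded patients counted as not cured in the all-treated analysis.

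Lower limit = d - 1.96 × √[p₁(1-p₁)/n₁ + p₂(1-p₂)/n₂], using whole-patient counts:

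| Excluded, Amphomul vs AmBisome | MITT counts | MITT lower limit | All-treated counts | All-treated lower limit |
|---|---|---|---|---|
| 2% vs 2% | 350/368 vs 116/122 | -0.044 | 350/375 vs 116/125 | -0.047 |
| 5% vs 2% | 338/356 vs 116/122 | -0.046 | 338/375 vs 116/125 | -0.081 |
| 8% vs 2% | 328/345 vs 116/122 | -0.045 | 328/375 vs 116/125 | -0.110 |

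Worked for 8% vs 2%, all treated: 0.875 - 0.928 = -0.053; SE = 0.0288; -0.053 - 1.96 × 0.0288 = -0.110. Without rounding to whole patients, the underlying difference is 0.95 × 0.92 - 0.95 × 0.98 = 0.874 - 0.931 = -0.057.

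With 90% cure among those retained, the MITT and all-treated lower limits are -0.064 and -0.094 at 5% vs 2%, and -0.065 and -0.122 at 8% vs 2%. The pattern is the same.

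**A severe case, 14% vs 2%.** All-treated cure is 0.95 × 0.86 = 0.817 vs 0.95 × 0.98 = 0.931, a difference of -0.114, beyond the margin. The probability of declaring non-inferiority is Φ[(0.10 + d)/SE - 1.96].
- MITT (322.5 vs 122.5, d = 0): SE = 0.0231, giving Φ(2.36) = 0.991.
- All treated (375 vs 125, d = -0.114): SE = 0.0302, giving Φ(-2.42) = 0.008.

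**The case against.** Several limits on this point are fair, and they stand.

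- A reader might infer that failures in general disappear. They do not. Parasitological failures at Day 30 or 45 have an efficacy assessment, and so do patients who relapse later. These are the events that definitive cure mainly measures. Only uncompleted infusions and exits before the Day 30 visit are affected.
- A reader might infer that any interrupted infusion is excluded. Sections 11.5 and 15.6.4 permit temporary interruption, and nothing says that an interrupted but completed infusion fails MITT. The opening condition in Section 17.2 asks only that drug was given and one efficacy assessment made. It is looser than Section 20.1, but Section 20.1 defines the set that is tested.
- Section 17.2 counts amastigotes on a splenic smear as failure, so a patient with +1 at Day 30 and 0 at Day 45 might seem to be both failure and cure. The same section sends +1 to Day 45 and a score of 0 there to follow-up, and Section 17 calls that initial cure. The list is loosely worded but sets no rival rule.
- Section 18.6 says "Progression of underlying disease/study indication/lack of efficacy of the IP should NOT be reported as an AE/SAE". A reader might infer that an early death from kala-azar could appear in no analysis. That is speculative: the sentence does not mention death, which is both a recorded withdrawal reason (Sections 12.6.1 and 12.6.3) and an SAE criterion (Section 18.1.3).
- The numbers may be small. Section 9.6 reports very few infusion-related events at this dose. Many DLTs rest on laboratory values scheduled at Day 7, after the infusion has ended. The 14% is an assumption. The planned 20% covers all dropout and major deviations over the whole study, so it does not support that figure.

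Daily clinical grading in hospital, also in Section 17.2, might be offered as an early efficacy assessment. That section itself places the first endpoint assessment at Day 30. If another reading is meant, the text has to say so.

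**Conclusion.** Wrong as written. The protocol fixes the sets for its primary test, and both leave out patients according to toxicity, death, rescue or loss before Day 30. Section 17.2 contradicts itself on discontinuation for intolerance and for a DLT.

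The size depends on imbalance between arms, which cannot be known in advance. Under the assumed rates, the conclusion is unchanged at 2% vs 2% and at 5% vs 2%. At 8% vs 2%, MITT passes and the all-treated analysis does not. The true difference of -5.7 points is then still inside the margin, so passing is not in itself a false conclusion, but MITT shows a difference of about zero. At 14% vs 2%, a product worse by more than the margin passes MITT in about 99% of trials, against about 1% when early exits count as non-cures. The documents do not support saying that the bias always favours Amphomul; that needs more early exits in its arm.

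**What to change.** In Section 20.2.2, run the primary non-inferiority test on all randomised patients, or at least on the existing ITT set (all dosed). Count as not definitively cured any patient with:

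- an infusion not completed for toxicity;
- death;
- rescue or another antileishmanial drug;
- withdrawal for an adverse event or lack of efficacy;
- no Day 30/45 assessment for any other reason (loss, consent withdrawal, investigator discretion), with a sensitivity analysis for this last group.

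Keep PP as the companion analysis and the current MITT as a sensitivity analysis. In Section 17.2, reconcile the non-evaluable statement with the intolerance item for analysis purposes. As tidy-up, align its failure list with the score table in Section 17. These are analysis classifications and change no patient's care.

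The cost is wording in Sections 17.2 and 20.1 to 20.2.2. Withdrawal dates and reasons are already collected, so no new data are needed. Cure rates and power fall somewhat. If 5% per arm become non-cures on a 90% cure rate, the rate is 0.90 × 0.95 = 0.855 and power at 375/125 is Φ(0.10/0.0364 - 1.96) = 0.785, about 79%. The comparison now is about 90% with nobody excluded (Φ(0.10/0.0310 - 1.96) = 0.898), or about 88% in an MITT of roughly 356/119.

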## Patient Completion and Withdrawal

### For each patient, according to the protocol, the study is deemed

- **Completed**

The patient will be administered study treatment as per the protocol, and completes all the safety and efficacy assessments on- Day 7, Day 30, Day 45 (only for patients with splenic aspirate score +1 on Day 30), and at 6 months after study drug administration.

- **Discontinued/withdrawn**- Withdrawal from the study can occur under the following circumstances:
  - 1. Death
    2. Adverse event
    3. Lack of efficacy (treatment failure)
    4. Patient consent withdrawal
    5. Investigator’s discretion
    6. Sponsor’s decision
    7. Pregnancy in a patient
    8. Lost to follow-up*

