**Visit 2- Day 30 (+/- 5 days):**

- A thorough clinical examination will be done.
- Splenic aspirate will be done to assess parasitological cure and will be graded in exactly the same manner as outlined above. The score will be assessed as follows:
  - 1. If the score is 0, then it is concluded as Initial cure achieved. Patient will be followed up till 6 months after study drug administration.
    2. If the score is +1 then repeat confirmatory splenic aspirate at 15^th^ day after Day 30 aspirate (i.e. Day 45 of study)
    3. If the score is above +1, then these patients will be considered as treatment failures and will be discontinued from the study & rescue medication will be given. No further follow‑up will be performed.
- Prothrombin time will have to be carried out before splenic aspiration and procedure will be done only if result is ≤4 seconds above the control
- Safety assessment (AEs, SAEs, IRTs, nephrotoxicity hepatotoxicity and laboratory values for different parameters) will be done
- Laboratory investigations done:-Hematology, Renal and Liver function tests, electrolytes as outlined in the screening section
- Vital signs will be recorded.
- Monitoring, recording and reporting for AEs, if any, will be done appropriately.
- Previous and concomitant medications will be recorded.
- Other laboratory investigations can be done, at the investigator’s discretion.

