**Visit 2 - Day 45 (Additional Visit, +/-5 days):**

- This visit will be done only for those patients who did not have complete parasitological cure on Day 30 and had a splenic aspirate score of +1. If the score is +1 and above, the patients will be considered as treatment failures and will be discontinued from the study and given rescue medication as deemed fit by the Investigator.
- A thorough clinical examination will be done.
- Splenic aspirate will be done to assess parasitological clearance. The score will be assessed as follows :

1. If the score is 0, then it is concluded as initial cure achieved. Patient will be followed up till 6 months after study drug administration.
2. If the score is +1 or above, then these patients will be considered as treatment failures and will be discontinued from the study and rescue medication will be given. No further follow-up will be performed.

- Prothrombin time will have to be carried out before splenic aspiration and procedure will be done only if result is ≤4 seconds above the control.
- Vital signs will be recorded.
- Patients who have parasitological clearance on Day 30 will not visit on Day 45.
- Laboratory investigations done:-Hematology, Renal and Liver function tests, electrolytes at investigator’s discretion.
- Monitoring, recording and reporting for AEs, if any, will be done appropriately.
- Previous and concomitant medications will be recorded.

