    - If blood samples from the patients are not drawn at the protocol-defined intervals, and in accordance with the methodology set in this protocol, the patient will not be considered as protocol compliant. However, given the study indication and underlying disease, this will not be reported as deviation of the protocol.

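### The per-protocol set, read with the protocol's own definition of completion, drops the treatment failures that the non-inferiority endpoint is meant to count

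*Protocol*

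**What the plan says.** Section 20.1 (Analysis Sets) gives the PP set as "All patients who complete the study visits per protocol without major protocol deviations". MITT is wider: patients dosed as specified who had at least one efficacy assessment.

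Section 12.6.1 says what completion means. A completed patient "completes all the safety and efficacy assessments on- Day 7, Day 30, Day 45" (the last only for a Day 30 score of +1) "and at 6 months after study drug administration". The same section lists "Lack of efficacy (treatment failure" among the reasons for discontinuation or withdrawal.

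Section 13 applies this to the smear results:
- Score above +1 at Day 30: "then these patients will be considered as treatment failures and will be discontinued from the study & rescue medication will be given".
- Score of +1 or above at Day 45: "then these patients will be considered as treatment failures and will be discontinued from the study and rescue medication will be given".

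Both items end follow-up. The rescue paragraphs in the Study Summary and Section 16.2 also discontinue a patient rescued for worsening Kala-azar.

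Section 20.2.2 makes initial cure a condition of definitive cure. It accepts non-inferiority if the lower limit of the two-sided 95% confidence interval for the difference in definitive cure exceeds -0.10, and adds: "Non-inferiority will be tested for both MITT and PP population".

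Section 19 says that if blood samples are not drawn on schedule, "the patient will not be considered as protocol compliant", and then that this will not be reported as a deviation.

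**The concern.** Membership of PP depends on the outcome that PP is used to analyse. A patient with a positive smear at Day 30 or Day 45 has failed on definitive cure, is withdrawn for that reason, and so does not complete in the sense of Section 12.6.1. Nothing in the protocol returns such patients to PP as failures.

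PP is normally included in a non-inferiority trial because poor adherence and deviations can make treatments look alike in a wider set. If PP instead removes failures, it makes the arms look alike itself and no longer serves as that check. The two sets could then disagree, with PP the misleading one. The trial is open-label, so an unsettled PP definition would be resolved with treatment assignments known.

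**Working it through.** **The plan's own figures.** The inflation reproduces: 400/(1 - 0.20) = 500, 300/0.80 = 375 and 100/0.80 = 125. The 400 cannot be checked directly, because Section 11.2 gives no reference cure rate. With equal rates p, margin 0.10, one-sided 0.025, 80% power and 3:1 allocation, the reference arm needs

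(1.96 + 0.8416)² × p(1 - p) × (1 + 1/3) / 0.10².

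At p = 0.893 this is 100, so the total is 400; at p = 0.90 it is 95, total 380. A reference cure rate near 90% is therefore a reasonable working assumption, but it remains an assumption.

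**Effect on the PP rate.** Let p be the true definitive cure rate and f the share of non-cures withdrawn as failures or for rescue. Then

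- PP cure rate = p / [p + (1 - p)(1 - f)]
- PP size = n × [p + (1 - p)(1 - f)]

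Assume p = 0.78 for Amphomul and 0.90 for AmBisome, a true difference of -12 points and so beyond the margin, with 300:100 patients before exclusion and f equal in both arms. For example, at f = 0.80: 0.78/(0.78 + 0.22 × 0.20) = 0.78/0.824 = 94.7%, and 0.90/(0.90 + 0.10 × 0.20) = 0.90/0.92 = 97.8%. The last column is from binomial simulation with the unpooled Wald interval and the Section 20.2.2 decision rule.

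| f | PP cure, test vs reference | Difference (points) | Expected PP size | PP alone declares non-inferiority |
|---|---|---|---|---|
| 0 (failures kept) | 78.0% vs 90.0% | -12.0 | 300 / 100 | about 0.4% |
| 0.25 | 82.5% vs 92.3% | -9.8 | 283.5 / 97.5 | about 2% |
| 0.50 | 87.6% vs 94.7% | -7.1 | 267 / 95 | about 13% |
| 0.80 | 94.7% vs 97.8% | -3.2 | 247 / 92 | about 93% |

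The total PP size falls to about 381, 362 and 339. The 20% allowance covers dropout and major deviations, not failures, so PP would fall short of 400 even if that allowance were met exactly.

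**Where the lost information sits.** Assume initial failure of 15% versus 5%, relapse of 5% of initial cures in both arms, and all relapses first found at the 6-month visit.

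- Failures counted: 0.85 × 0.95 = 80.7% versus 0.95 × 0.95 = 90.2%. The difference is -9.5 points and the lower limit -16.8, so non-inferiority is not shown.
- Completers only (255 and 95 patients): 95.0% versus 95.0%. The difference is 0 and the lower limit -5.1, so non-inferiority is shown.

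The whole Day 30/45 component of the endpoint has left the comparison.

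**The case against.** **The PP wording can be read another way.** A Day 30 or Day 45 failure has attended every visit that the protocol requires of that patient, so could be said to have completed the visits per protocol. Section 20.1 does not refer to Section 12.6.1, and Section 17.2 treats a patient with one efficacy assessment as eligible for efficacy evaluation and a positive smear as treatment failure. This reading is possible. It runs against the only definition of completion in the document, which requires the 6-month assessment and puts treatment failure on the other side. That is a reason to settle the wording.

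**MITT protects the decision.** This largely stands. If both sets must succeed, the trial cannot declare non-inferiority more often than MITT does, which is about 0.4% in the 78% versus 90% case if MITT keeps every failure. A reader might infer from the 93% that the trial would probably make a false claim; the documents do not support that. The protocol does not say, however, that both sets must succeed.

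**PP still detects some inferiority.** A reader might also infer that PP passes automatically. It does not: the result depends on the share withdrawn, which the protocol does not give. At 25% withdrawn, false acceptance is about 2%, within the nominal 2.5%.

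**Not every failure leaves PP.** A relapse first found at the 6-month visit stays in as a failure. So could one found earlier, since aspiration is allowed at 6 months or earlier and discontinuation follows the decision to rescue, not detection of the relapse. It would go too far to say that only relapses found at the last visit can count.

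**Section 19.** Off-schedule sampling is expressly not reported as a deviation, so it need not trigger the major-deviation exclusion. Calling PP membership undefined on this ground alone would overstate what is a conflict of wording.

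**Conclusion.** The point holds. On the protocol's own terms PP is selected partly on the endpoint tested in it: Day 30/45 smear failures and patients discontinued for rescue drop out, cure rates rise in both arms and a true difference is shrunk. How far depends on the share of non-cures withdrawn. Under the assumed rates, false acceptance in PP alone runs from about 2% to 93% as that share goes from 25% to 80%, against about 0.4% with failures kept. These figures assume the same share in both arms and no other selection into PP.

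The consequence is a weakened PP half of the non-inferiority test, not a demonstrated inflation of the trial's overall error rate. The Section 19 conflict is separate and minor.

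**What to change.** In Section 20.1, define PP as patients without major protocol deviations who either completed the 6-month visit or reached a protocol-defined failure (Day 30/45 smear failure, relapse, or discontinuation for rescue), and state that such failures count as not cured.

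In Section 19, reconcile the statement that a patient with off-schedule blood sampling is not protocol compliant with the statement that this is not reported as a deviation, so that the patient's PP status is clear.

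The cost is small: one sentence in each place, and PP cure rates that are less favourable in both arms. Smear scores and withdrawal dates and reasons are already recorded, so no new data are needed, and no visit, treatment or rescue rule changes.
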